## Abstract

**Objective:**

To evaluate the effectiveness of personalized and home-based speech therapy on quality of life, intelligibility, and social participation for people with Parkinson’s disease (PD) who have a reduced intelligibility of speech.

**Background:**

Speech problems in PD have a profound negative impact on social interaction and quality of life. Evidence for speech therapy in PD is growing, but more work remains needed to explore its full potential. Efficacy exists for highly intensive standardized speech treatment programs, but not all patients can comply with this rather intense intervention, especially the more severely affected ones. Here, we aim to study the effectiveness of personalized and home-based (remote) speech therapy in PD on quality of life and speech. The intervention will be supported by a dedicated speech training app. We expect that this approach will improve speech intelligibility and quality of life in patients irrespective of disease stage.

**Methods:**

We will perform a single blind, randomized controlled trial, comparing 8 weeks of speech therapy to no intervention using a waiting list design. A total of 215 PD patients with problems in intelligibility will be recruited by 12 highly experienced speech therapists. All patients will be measured at baseline and after 8 weeks (primary endpoint). Additionally, the experimental group will be re-assessed one more time, after a wash-out period of 24 weeks. The control group will receive deferred treatment after 8 weeks, but without additional follow-up assessments. Our primary outcome is quality of life (as measured with PDQ-39). Secondary outcomes include speech and voice quality, intelligibility, severity of voice and speech complaints, and caregiver burden.

**Results:**

The inclusion of participants has started on March 1, 2019, and is expected to be finalized on April 1, 2021. We expect to have the first results in January 2022.

**Conclusions:**

We will investigate the effectiveness of speech therapy in PD. Particular strengths of our study include a randomized and single-blinded design, the personalized treatment approach, the inclusion of PD patients irrespective of disease stage or severity of the speech complaint, the long-term follow-up, the adequate power, and the use of a patient-relevant primary endpoint. This will allow us to draw firm conclusions about the effectiveness of personalized and remote speech therapy for PD patients in all disease stages.

**Trial registration:**

ClinicalTrials.govNCT03963388. Registered on May 24, 2019

## Background

Parkinson’s disease (PD) is a progressive neurological disorder, with a large variety of motor and non-motor problems, including reduced speech intelligibility which may occur in up to 70% of patients [1]. Even patients without explicit intelligibility problems can have difficulties conducting a routine conversation. Reduced intelligibility and poor communication skills can have a profound negative impact on social interaction and quality of life [2]. Since pharmacological treatment only has limited beneficial effects on speech [3, 4], speech therapy is particularly relevant to improve speech quality and to enhance intelligibility.

Currently, there is level II evidence to support existing speech treatment programs in PD [5, 6]. The most recent Cochrane reviews from 2012 on this subject showed that evidence is growing, but more work remains to explore its full potential due to small sample sizes, inadequate methodology, lack of outcomes relevant to PD patients, and insufficient follow-up to determine the duration of any improvement [6, 7]. Since 2012, three further RCTs have been initiated [8–10], all aiming to evaluate Lee Silverman Voice Treatment LOUD (LSVT-LOUD) versus another or no treatment in a small sample (20 and 30 patients per treatment arm).

It seems that current speech treatments that show positive outcomes are not suitable for all PD patients: LSVT-LOUD [10–12], Pitch Limiting Voice Treatment [13], and Speak Out [14] are all highly intensive (3–4 times a week in a professional setting, plus home exercises) and generally follow the same program for all patients. A recent LSVT analysis reported that, in routine care, some patients refuse this high-intensity treatment or do not adhere to the entire protocol because of physical limitations or fatigue, suggesting that this intensive approach is most suitable for only a select group of patients [15]. Offering treatment remotely (i.e., delivered at home) may be an attractive solution to increase treatment intensity, while reducing travel burden. Recently, studies using telerehabilitation have shown the feasibility of online delivery of speech therapy in small samples of PD patients [16, 17], but dedicated speech therapy is still not available for many PD patients, in particular, for those with advanced PD.

In addition to the research challenges mentioned above, it is also common to experience various unmet challenges related to speech therapy in PD itself. First, although it is relatively easy to temporarily increase intelligibility in PD patients with the right instruction, it takes intensive exercise and specific feedback for patients to get used to normal loudness again and to apply it independently in an everyday conversation. A second challenge is that speech exercise can make speech more intelligible, but patients may remain dependent on cueing. It is uncertain how to deliver such cueing at home, outside the therapeutic settings. Thirdly, conveying a message through speech requires producing both comprehensible language and intelligible speech at the same time. This dual tasking becomes increasingly difficult for patients with PD [18], making them progressively more dependent on caregivers. To help patients to monitor their speech, we have developed a sophisticated app, namely the Voice trainer [19], that provides real-time visual feedback aiming to improve intelligibility. Several user tests were conducted with both patients and speech therapists to optimize the usability of the application and before introducing and implementing the app in the training of speech therapists in the Netherlands. In this study, patients use the voice trainer to practice their speech quality and maintain their intelligibility during daily conversation and social interaction as well.

In an experimental design, our main aim is to address all these challenges by evaluating a multifaceted approach of home-based speech therapy in a single-blind, randomized, and controlled trial, using quality of life as the primary outcome. Specifically, our approach combines the following elements: (1) personalized treatment, based on (internationally) established speech treatment programs and guidelines [20, 21], making speech therapy available for every PD patient regardless of disease stage; (2) consistent use of the Voice Trainer app to enable cueing during treatment and outside the therapeutic setting; and (3) treatment delivery within the patients’ home using telerehabilitation and delivered by highly experienced therapists who work as part of the Dutch ParkinsonNet (a professional network of allied health therapists with dedicated expertise in the management of PD [22, 23]), to enable patients to follow the program with adequate intensity at home.

We expect an improvement in both quality of life (primary outcome) and speech quality (secondary outcome) for patients across all disease stages. Moreover, we hypothesize that improvements will be maintained at follow-up, since long-term effects in improvements of speech in PD have been found in previous studies [10]. Therefore, our primary objectives are (1) to study the effectiveness of personalized speech therapy on quality of life in patients with Parkinson’s disease and (2) to explore whether the effects of speech therapy remain after long-term follow-up (6 months).

## Methods/design

### Trial design

Here, we will perform a single-blinded randomized controlled trial comparing speech therapy to no intervention using a waiting list design. We opted for this design because this enables us to properly compare patients who have received therapy with patients who have not received therapy (yet), thereby answering our primary research question addressing the effectiveness of speech therapy in patients with PD. The control group receives deferred treatment directly after reassessment, which is a realistic waiting period in usual care. Patients will be assigned to either the experimental group or the control group in a 1:1 manner, by means of a computerized validated variable block randomization model using Castor EDC [24] with automatically generated block sizes of 4, 6, and 8. Stratification will take place for gender, speech therapist, Hoehn and Yahr stage, and age (< 46 years, 47–55 years, 56–65 years, > 66 years). To ensure blinding, allocation of the participants is made invisible for assessors in the data collection program Castor EDC. Furthermore, patients and speech therapists are instructed to refrain from discussing the treatment with the assessors. Measurements will be performed at baseline (T0) and after 8 weeks (T1). For the intervention group only, an additional follow-up measurement takes place 32 weeks after baseline (T2) (Fig. 1) to study whether the effects are retained at the long term. The T1 measurement is the primary endpoint at which we will compare the intervention group with the control group. The T2 measurement is the secondary endpoint at which we will compare the within-group differences of the intervention group after follow-up.

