### Procedure

Patients are asked to participate by highly experienced speech therapists, and we will recruit these speech therapists throughout the Netherlands, using the nationwide ParkinsonNet infrastructure [23]. ParkinsonNet is a national health care model that consists of 70 regional networks, with over 3000 health professionals with specific expertise in the treatment of PD patients [22]. Twelve speech therapists who participate in ParkinsonNet will be selected based on their caseload, who will each treat 16–20 patients, which is approximately 1 patient per month during the inclusion period.

During the first visit, speech therapists inform eligible patients about the study with a formal information letter. The speech therapists explicitly do not give any therapeutic advice to patients during this first visit, since patients can already benefit from education. To provide the patients enough time to consider participation, the research team calls the patients after 7 days to verify their willingness to participate and to check for eligibility. When a participant is willing and eligible, the baseline measurement (T0) is scheduled. One day after baseline measurement, randomization is performed by a researcher who is not involved in any of the measurements and who also subsequently informs both the therapist and patient about the group allocation. If the patient is allocated to the intervention group, treatment will start within a week. If the patient is allocated to the control group, treatment will start after the second measurement (T1), as shown in the flowchart (Fig. 1).

The intervention is delivered during a maximum period of 8 weeks. The number of sessions depends on the complexity of goals and possibilities of the patient (i.e., time and availability). Between T1 and T2 (only for the intervention group), patients will not receive speech therapy but still can use the Voice Trainer app.

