### Participants

Eligible patients have PD according to the MDS criteria [25] as confirmed by their own treating neurologists. Other inclusion criteria are (1) reduced intelligibility bothering daily communication according to the patient and/or informal caregiver(s), (2) a desire to improve their speech, and (3) willingness and ability to receive online treatment. Importantly, patients who do not own a device that is suitable for online treatment can still participate in the study, because in those cases, we will provide them with a loan device. The exclusion criteria are (1) recently received (< 1 year) speech therapy, (2) voice or speech problems due to other causes, (3) communication difficulties based on language problems without predominantly reduced intelligibility, and (4) (technical) inability to receive online treatment. Patients are not excluded by disease stage or the severity of their speech complaint, because we aim to study the effectiveness of the intervention irrespective of dysarthria severity.

The drop-out criteria are (1) withdrawal from consent and (2) health problems of such severity that conducting assessments is not possible. When willing and available, a primary informal caregiver of each patient can participate in the study by completing two questionnaires about speech and caregiver burden. Inclusion will take place over a period of 25 months, starting on March 1, 2019, and ending on March 31, 2021. Informed consent of both patient and caregiver (when applicable) is obtained by the researcher before the baseline assessment.

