### Sample size calculation

Based on a trial on the effectiveness of multidisciplinary care [50], we have calculated the sample size on our primary outcome with a conservative estimated PDQ-39 total score improvement of 2.5 points (SD = 5.8) in the intervention group, and no difference in controls. This estimated improvement exceeds the minimally important difference of 1.6 points [33]. A sample of 170 patients would be needed to show this expected difference. Allowing for 20% drop-out, we will include 215 patients.

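### Blocks of 4 to 8 within an estimated 192–480 strata for 215 patients secure little balance; the ANCOVA omits two randomisation factors (therapist, gender), and the printed age bands skip ages 46 and 66

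*Protocol article*

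**What the plan says.** All of the following is in the protocol article.

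- **Allocation ratio (Trial design):** "Patients will be assigned to either the experimental group or the control group in a 1:1 manner".
- **Blocks (Trial design):** variable blocks, generated in Castor EDC, with "automatically generated block sizes of 4, 6, and 8".
- **Strata (Trial design):** "Stratification will take place for gender, speech therapist, Hoehn and Yahr stage, and age". The bands are given as "age (< 46 years, 47–55 years, 56–65 years, > 66 years". The number of Hoehn and Yahr categories is not given, and neither minimisation nor merging of strata is mentioned.
- **Therapists (Procedure):** "Twelve speech therapists who participate in ParkinsonNet will be selected based on their caseload, who will each treat 16–20 patients". The same section has therapists approach the patients and has a researcher tell therapist and patient the allocation.
- **Range of disease (Participants):** "Patients are not excluded by disease stage or the severity of their speech complaint".
- **Size (Sample size calculation):** "we will include 215 patients".
- **Model (Analysis effectiveness):** ANCOVA with group as factor and four covariates: the baseline value, age, Hoehn and Yahr stage and disease duration. Therapist and gender are not listed.
- **Timing (Trial status):** inclusion ended in March 2021, with follow-up measurements running to November 2021.

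**The concern.** Permuted blocks secure balance only when they fill. With one block sequence per combination of four factors, a therapist's 16 to 20 patients are scattered over 16 to 40 cells, and even the smallest block needs four patients in the same cell. Most blocks are then cut off after one or two patients, and little of the intended balance on any factor is obtained.

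This matters most for therapist and gender. Age and stage are picked up again in the ANCOVA; these two are not. The article's Discussion itself names variation between therapists as its first challenge.

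Separately, a printed allocation rule with no band for two ages cannot be followed as written. A reader cannot tell how those patients were stratified.

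**Working it through.** **The plan's own figure.** The article states no number of strata. Its sample size can be reproduced. With a difference of 2.5, SD 5.8, and two-sided 5% and 80% power (assumed, not stated), n per arm = 2 × (1.96 + 0.842)² × 5.8² / 2.5² = 84.5, so 85 per arm and 170 in total. Then 170 / 0.80 = 212.5, or 213, against 215 stated. The size is not in dispute.

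**Number of strata.** Stated inputs: 12 therapists, 4 age bands, N = 215. Assumed: 2 genders, and 2, 3 or 5 Hoehn and Yahr categories.

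- 5 categories: 2 × 12 × 5 × 4 = 480; 215 / 480 = 0.45 patients per stratum
- 3 categories: 2 × 12 × 3 × 4 = 288; 215 / 288 = 0.75
- 2 categories: 2 × 12 × 2 × 4 = 192; 215 / 192 = 1.12

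**Simulated balance.** Permuted blocks of 4, 6 or 8 (equally likely, assumed) within each stratum; 215 patients, therapists equally likely; 800 runs per row. The case mixes are assumptions, since the article gives none:

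- even: all levels of each factor equally frequent
- skewed: gender 65/35, stage 10/55/25/8/2% (65/35% with two categories), age bands 2/8/30/60%
- very skewed: gender 70/30, stage 5/70/20/4/1%, age bands 1/5/24/70%

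D is the difference in arm sizes. Under simple randomisation its variance is 215, so its SD is √215 = 14.7.

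| Scheme and mix | Strata | Occupied | Patients in completed blocks | SD of D | Variance of D relative to simple |
|---|---|---|---|---|---|
| 5 stages, even | 480 | 174 | 0.3% | 14.1 | 92% |
| 5 stages, skewed | 480 | 120 | 10% | 12.6 | 74% |
| 5 stages, very skewed | 480 | 94 | 24% | 10.4 | 50% |
| 3 stages, even | 288 | 151 | 1.3% | 13.5 | 85% |
| 2 stages, skewed | 192 | 94 | 17% | 11.2 | 58% |
| Therapist only | 12 | 12 | 85% | 3.9 | 7% |

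**Balance within therapist.** Under simple randomisation the root-mean-square difference per therapist is √(215/12) = 4.2 patients. The simulated variance ratios within therapist for the first five rows run from 0.54 to 0.92, which gives √(0.54 × 17.9) = 3.1 to √(0.92 × 17.9) = 4.1. Therapist-only blocks (ratio 0.07) give 1.1.

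**What unequal arms cost.** Relative efficiency is 1 − (D/N)². For D = 28 that is 1 − (28/215)² = 0.983. For power, scale D to 170 evaluable patients and use the normal approximation:

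- D = 0: 80.2%
- D = 16 (12.7 after scaling): 80.0%
- D = 28 (22.1 after scaling): 79.6%

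The loss is at most about 0.7 points.

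**Age bands.** In whole years, 46 is neither below 46 nor within 47–55, and 66 is neither within 56–65 nor above 66. No assumption is needed.

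**The case against.** The strongest case on the other side is that the harm is slight and partly dealt with already. Several parts of it stand.

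- **Small power cost.** This stands, as shown above. Allocation remains 1:1 in expectation and no bias follows.
- **Age and stage are in the ANCOVA.** This stands, and narrows the point to therapist and gender.
- **The count of 480 rests on five stages.** This stands. The grouping may be set in the full protocol or in Castor. The conclusion nevertheless holds across two to five categories.
- **Therapist matters less than it seems.** Controls start treatment only after the 8-week measurement, so until then therapist skill acts in one arm, and for controls the therapist is only a source of recruitment. This stands in part. A therapist term accounts for differences between recruitment sources, but balancing or adjusting for therapist does not remove therapist clustering within the treated arm.
- **Therapist-only blocks have a drawback.** This stands. Therapists recruit and learn each allocation. If a recruiter tracks allocations and always guesses the under-represented arm, correct guesses are about 67% with therapist-only blocks, against about 55% under the present scheme (an upper bound, for a tracker who knows each patient's stratum).

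A reader might infer more than the documents support. One inference is that the scheme is equivalent to simple randomisation; the simulated variance is 50–92% of that under simple randomisation, so there is some gain. Another is that the article claims a balance it lacks; it lists factors and a ratio and asserts no achieved balance. A third is that a 66-year-old could not be randomised; allocation was computerised, and the coding may differ from the printed bands.

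**Conclusion.** The point holds in a limited form. With two to five stage categories assumed, the stratification balances arm sizes and therapists only slightly to moderately better than simple randomisation: SD of the arm difference about 10 to 14, against 14.7 for simple and about 4 for therapist-only blocks. The exact value depends on the assumed case mix; the sparseness does not. The consequence is weak balance within therapist and gender, two randomisation factors that the primary model then leaves out. It is not a threat to validity, and the power loss from unequal arms is under 1 point. The gap at ages 46 and 66 is a plain error in the printed rule. Both are worth correcting because the corrections are nearly free.

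**What to change.** The Trial status section reports inclusion as finished, so the allocation scheme can no longer be changed. (Table 2 still lists the trial as recruiting and should be brought into line.) Before the analysis:

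1. In Analysis effectiveness, add therapist (random or fixed effect) and gender to the primary model, so that all four randomisation factors are adjusted for.
2. Report the achieved allocation per therapist, and by gender.
3. In Trial design, state the Hoehn and Yahr categories used, print contiguous age bands as actually coded in Castor, and say how patients aged 46 and 66 were assigned.

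The cost is a few sentences and some degrees of freedom: 11 for therapist as a fixed effect, or one variance component as a random effect, plus one for gender.

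Had inclusion still been open, minimisation with a random element would be preferable to therapist-only blocks, because recruiting therapists are told each allocation and could follow a therapist-level sequence.

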**Fig. 1 Fig1:**
[figure not shown]
Flowchart of the design and enrollment procedures

Full ethical approval has been granted by the medical ethical committee of Arnhem-Nijmegen (NL67867.091.18), and the PERSPECTIVE trial is registered at ClinicalTrials.gov (NCT03963388) on May 24, 2019. Important protocol modifications will receive a written notice to the relevant parties (medical ethical committee, trial register, speech therapists, and/or participants).

### Procedure

Patients are asked to participate by highly experienced speech therapists, and we will recruit these speech therapists throughout the Netherlands, using the nationwide ParkinsonNet infrastructure [23]. ParkinsonNet is a national health care model that consists of 70 regional networks, with over 3000 health professionals with specific expertise in the treatment of PD patients [22]. Twelve speech therapists who participate in ParkinsonNet will be selected based on their caseload, who will each treat 16–20 patients, which is approximately 1 patient per month during the inclusion period.

During the first visit, speech therapists inform eligible patients about the study with a formal information letter. The speech therapists explicitly do not give any therapeutic advice to patients during this first visit, since patients can already benefit from education. To provide the patients enough time to consider participation, the research team calls the patients after 7 days to verify their willingness to participate and to check for eligibility. When a participant is willing and eligible, the baseline measurement (T0) is scheduled. One day after baseline measurement, randomization is performed by a researcher who is not involved in any of the measurements and who also subsequently informs both the therapist and patient about the group allocation. If the patient is allocated to the intervention group, treatment will start within a week. If the patient is allocated to the control group, treatment will start after the second measurement (T1), as shown in the flowchart (Fig. 1).

The intervention is delivered during a maximum period of 8 weeks. The number of sessions depends on the complexity of goals and possibilities of the patient (i.e., time and availability). Between T1 and T2 (only for the intervention group), patients will not receive speech therapy but still can use the Voice Trainer app.

